### Secondary outcomes

Secondary outcomes will include changes in educator physical activity practices related to role modelling physical activity (e,g., I join children in physically active play), programming and planning physical activity (e.g., I incorporate physical activity into room routines and transitions), promoting and encouraging physical activity (e.g., I talk with children about the importance of physical activity), and not using physical activity for managing misbehaviour (e.g., I take away five or more minutes of active play time if children misbehave). These practices will be assessed with a total of 30 items sourced from the NAPSACC instrument, EPAO instrument or developed specifically for purposes of this trial to align with the practices outlined in the physical activity policy template [31–33]. All items are assessed on a six-point Likert scales from Never (1) to Always (6) in the educator survey administered at baseline and post-intervention.

Secondary outcomes will also include changes in educator self-efficacy (eight items; e.g., I feel able to provide children with opportunities for energetic play throughout the day) and motivation (eight items; e.g., I am motivated to provide children with opportunities for energetic play throughout the day), with items aligned specifically with the Play Active policy template recommendations. Changes in educators attitudes and beliefs towards children’s physical activity and sedentary behaviour will be assessed using nine items developed to be fit-for-purpose based on the key barriers and enablers for implementing a physical activity policy in ECEC identified through the Delphi process [13]. Changes in educator-perceived social support provided by management and co-workers for encouraging physical activity and limiting sedentary behaviours will be assessed with four items. The above items are all context-specific to the Play Active program and consistent with standard types of physical activity items measured on seven-point Likert scales from Strongly Disagree (1) to Strongly Agree (7) [34–36].

Service directors will be surveyed at baseline and post-intervention to collect information on changes in the degree to which the ECEC physical environment supports young children’s physical activity using established items from the EPAO’s space, equipment and environment subscale [32], which has been modified for the Australian ECEC context and shown to provide reliable measures [33].

Given the short three-month policy implementation period for this trial, it is unlikely there will be a significant change in children’s physical activity. However, to ensure we capture any potential changes, data will be obtained from the Energetic Play Assessment Tool, which will be used both as an implementation support strategy and a data collection tool.

### Process outcomes

To understand the mechanisms by which policy implementation support strategies did or didn’t work, process evaluation outcomes will be measured post-intervention for intervention service directors and educators [37, 38]. Survey measures will include the reach of the implementation support strategies, the acceptability and appropriateness of the Play Active program (policy and implementation support strategies) and educator feedback on adaptations to improve the program.

Uptake of the implementation support strategies (reach) will be measured using multiple methods. These include project management logs to see if the policy template is returned for review; website data from partners (Nature Play WA and KIDDO) to assess the uptake of professional development by educators as well as self-report items in the educator post-intervention survey. To further assess reach, educators will also be asked whether their service has a physical activity policy and how often they used the resource guide (assessed on a seven-point Likert scale from once (1) to more than once per day (7)). To assess knowledge of the Play Active program, educators will also be asked a series of true/false knowledge questions based on the content of the physical activity policy recommendations (coverage).

Director- and educator-reported satisfaction (acceptability) with the Play Active program, including open ended questions about what they liked most and what could be improved will be collected. The educator post-intervention survey will also include items on the usefulness (appropriateness) of the resource guide and professional development (assessed on a five-point Likert scale from not at all useful (1) to extremely useful (5)), and what they liked most (acceptability) and what could be improved (suggested adaptations).

### Participant response and retention

All services will take part in baseline and post-intervention data collection according to the schedule in Table 1. Director and educator surveys will be administered online using the secure REDCap survey platform [39, 40]. Survey links will be emailed to all service directors and educators with reminders sent via the REDCap platform, email and telephone. Service directors will be contacted weekly via phone or email to remind them to complete their survey and to encourage their educators to complete their survey. Hard copy and PDF director and educator surveys will also be made available to assist with survey completion. Baseline and post-intervention educator surveys will be linked through the REDCap platform via unique participant codes, so that matching of repeat measures is automatic. Any data resulting from hard or soft copy surveys will be double entered into a Microsoft Excel spreadsheet by two different research team members. A third team member will confirm discrepancies and amend as required. Participant data will be managed on a secured electronic database (REDCap) and hard-copy forms stored securely at the research facility.

Well-established retention strategies such as contacts via email, phone calls and face to face visits will be used to thank services for their participation to date and remind them to complete all components of data collection so as to minimise attrition at post-intervention data collection.

### Statistical analysis

Analysis will be undertaken following intention-to-treat principles. To examine the representativeness of the study sample, service-level characteristics will be compared with the full sampling frame of Perth and Peel ECEC services at the time of recruitment using data available from Australian Children’s Education and Care Quality Authority [28]. The primary outcome variables of educator-reported frequency and time provided for children to be physically active will be analysed using generalised linear mixed effects models and will include fixed effects for socio-demographics, time, intervention, time-by-intervention interaction, and random effects for individual educators nested within services. Factor analysis and latent class analysis will be considered for secondary outcome items prior to being similarly analysed using generalised linear mixed effects models. Open-ended, qualitative data responses to process outcome items in the post-intervention director and educator surveys will be thematically analysed according to a prepared coding framework and consensus reached by at least two research team members not involved with data collection. For any discrepancies, a third team member will make the final decision. Other process evaluation data will be summarised descriptively. All quantitative data preparation and analyses will be carried out using SAS 9.4 or above and Stata 17 or above, and qualitative analysis using NVivo 20.0 or above.

As part of dissemination, a study report presenting the overall findings of the research will be prepared for all participants and stakeholders. Peer-reviewed publications and presentations will allow the results to be disseminated to the scientific community. Results will be reported according to Consolidated Standard of Reporting Trials guidelines [26].

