### Sample size and power

Based on a 15 min per day change in the primary outcome variable (i.e., average change in educator reported time allocated for children to be physically active indoors and outdoors), this trial will require a total of 60 services with 108 educators per group (80% power, 2-tailed alpha level of 0.05) to detect a moderate effect size of 0.4. After adjusting for clustering of educators within services, an educator ICC of 0.01–0.05 and a 30% dropout at follow-up data collection, 309 educators (6 per service) from 60 services will be recruited. This represents 11% of long-day care services in the Perth, Western Australia region.

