### Randomisation

Services will be randomised to the intervention or wait-listed comparison group after baseline data collection. Using a central randomisation procedure, the randomisation sequence will be generated using a computerised random number function in Microsoft Excel. Due to the increased chances of contamination between services of the same provider if allocated to different groups, these services will be randomly allocated to the same group or two different groups grouped by geographical location. The research team member generating the allocation sequence and assigning services to their group will not be involved with recruitment, data collection or intervention delivery. Due to the nature of the intervention (i.e., implementation of a policy), it is impossible to blind services to their group allocation, thus this will be an open trial without masking and services will be aware of the group they are assigned to.

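### The primary model estimates a baseline arm difference that randomisation has already set to zero in expectation, and so gives up precision it could keep at no cost

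*Protocol article*

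**What the plan says.** Order of events (Randomisation): "Services will be randomised to the intervention or wait-listed comparison group after baseline data collection".

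Primary model (Statistical analysis): the outcomes "will be analysed using generalised linear mixed effects models", with "fixed effects for socio-demographics, time, intervention, time-by-intervention interaction" and "random effects for individual educators nested within services". Neither a baseline-outcome covariate nor a constraint of equal baseline means is stated.

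Data (Participant response and retention): there are two waves, since "All services will take part in baseline and post-intervention data collection according to the schedule in Table 1". Educator surveys are linked by participant code, "so that matching of repeat measures is automatic".

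Sizing (Sample size and power): "Based on a 15 min per day change in the primary outcome variable", with the aim "to detect a moderate effect size of 0.4". The section assumes an ICC of 0.01 to 0.05 and 30% dropout.

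**The concern.** With two waves and time coded 0 at baseline, the four mean parameters (intercept, time, intervention, interaction) fit a separate mean for each arm at each wave. The intervention coefficient is the baseline difference between arms and the interaction is the difference in change. Because services are allocated only after baseline is measured, the true baseline difference is zero in expectation, and the model spends information on estimating it.

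Two things follow. The effect estimate is noisier than it need be. And when the arms happen to differ at baseline by D, the interaction subtracts the whole of D, although without clustering only about r × D would be expected to persist at follow-up. It therefore over-corrects by about (1 − r) × D. Socio-demographic covariates do not do the work of the baseline outcome.

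This is a comment on terms the protocol lists, not on detail left to a statistical analysis plan. The same model serves every primary outcome.

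**Working it through.** **Inputs.** From the protocol: 60 services (30 per arm if split equally), 309 educators, ICC 0.01 to 0.05, 30% dropout, effect size 0.4, 80% power, two-sided 5%. Assumed, because the protocol does not give it: r = 0.3, 0.5, 0.7. Also assumed: an identity link, and a service effect that is constant over the two waves.

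**1. The plan's own figure.** Per arm, 2 × (1.96 + 0.842)² / 0.4² = 98.1, so 99. With 309/60 = 5.15 educators per service and an ICC of 0.02 (inside the stated range), the design effect is 1 + 4.15 × 0.02 = 1.083, and 99 × 1.083 = 107.2, so 108. Then 216/0.70 = 308.6, so 309. The stated size reproduces, and it assumes no gain from baseline data.

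**2. Complete pairs, no clustering.** Take one measurement to have variance 1.
- Free baseline (difference in change): 2(1 − r) per educator.
- Common baseline, or baseline as a covariate: 1 − r².
- Ratio: (1 + r)/2 = 0.65, 0.75, 0.85, a reduction of 35%, 25%, 15%.

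**3. Complete pairs, with clustering.** For service size m, replace r by r* = (r + (m − 1)ICC)/(1 + (m − 1)ICC). With m = 5 and r = 0.5:
- ICC 0.01: r* = 0.54/1.04 = 0.519, ratio 0.760.
- ICC 0.05: r* = 0.70/1.20 = 0.583, ratio 0.792.

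Exact generalised least squares for 30 services per arm agrees. The planned interaction has variance 0.01333, identical to the change-score variance. The common-baseline model gives 0.01013 and 0.01056.

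**4. Dropout, no clustering.** With a fraction p of educators followed up, the ratio becomes (1 + r)/[(1 + r) + (1 − r)p]. The loss narrows because the planned mixed model also uses educators who have only a baseline. At the plan's p = 0.70:
- r = 0.3: 1.3/1.79 = 0.726
- r = 0.5: 1.5/1.85 = 0.811
- r = 0.7: 1.7/1.91 = 0.890

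**5. Clustering and dropout together.** Generalised least squares with 5 educators falling to 4, 6 to 4, and 5 to 3 per service (20%, 33% and 40% lost), at ICC 0.01 and 0.05. Power is Φ(2.80/√ratio − 1.96), starting from a nominal 80%.

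| r | Variance ratio | Reduction | Power |
|---|---|---|---|
| 0.3 | 0.710 to 0.795 | 20-29% | 88-91% |
| 0.5 | 0.797 to 0.860 | 14-20% | 86-88% |
| 0.7 | 0.881 to 0.920 | 8-12% | 83-85% |

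For example, at r = 0.5 and ICC 0.01 with 6 falling to 4, the planned model has variance 0.01526 and the common-baseline model 0.01262, a ratio of 0.827. In educators, the extremes are 1/0.920 − 1 = 9% and 1/0.710 − 1 = 41% more.

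**6. Over-correction, illustrated.** If the arms differed by chance by D = 10 minutes at baseline (assumption) and r = 0.5, the interaction would be shifted by about (1 − 0.5) × 10 = 5 minutes, ignoring clustering.

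**The case against.** The planned model is a standard and valid analysis of a two-wave cluster trial. It also matches the sizing, which is framed on change and reproduces without any benefit from baseline. All of that stands: what is at issue is efficiency.

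Several stronger readings are tempting but are not supported.

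- **That the analysis is biased or the trial underpowered.** Over repeated randomisations the interaction is unbiased; the over-correction is conditional on an observed imbalance. If 0.4 is scaled by the SD of change, the planned contrast has its nominal 80%. A shortfall needs 0.4 to be scaled by the SD of a single measurement and r below 0.5. At r = 0.3, ignoring clustering and dropout, power would then be about 66%, against 84% with a common baseline. The protocol does not say which SD is meant.
- **That the saving is 35%, 25% or 15%.** Those figures need complete pairs, no clustering and an identity link. The protocol plans for dropout and clustering, and its items are categorical.
- **That r is known to be moderate.** No r is given. The only related remark is that the items have acceptable repeatability. At r = 0.8 or 0.9, even complete unclustered pairs save only 10% or 5% of the variance.
- **That imbalance is likely because whole providers are allocated together.** The Randomisation section allows a provider's services to be divided between the groups by location, and Study design and setting puts single-service providers at 81%. Likelihood of imbalance cannot be quantified from this.
- **That only a constrained model keeps educators with one wave.** The planned mixed model keeps them too.

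**Conclusion.** The point holds as an avoidable loss of precision, together with over-correction for whatever chance imbalance occurs. It is not a finding of invalidity or of a wrong sample size. The direction is the same at every correlation tested (0.3 to 0.9).

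The size rests on an r that the protocol does not supply, on a linear scale and on stable service effects. Within r of 0.3 to 0.7 and the trial's own ICC range, with 20 to 40% lost, the planned model's effect variance could be cut by between 8% and 29%. For an ordinal or logit model these figures are approximate, and the equivalence to a change-score analysis is exact only for an identity link with complete pairs.

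The change is worth making because the linked baseline data are already being collected.

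**What to change.** Remove the intervention main effect from the primary model. Code time as 0 at baseline and 1 at follow-up, let both arms share one baseline mean, and define the treatment effect as the time-by-intervention term at follow-up. Keep the educator and service random effects, the socio-demographic covariates, and all educators with at least one wave. State this before outcomes are analysed by arm, and apply the same form to each primary outcome.

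Modelling the follow-up response with the baseline response as a covariate is second best. It loses educators missing either wave unless values are imputed, which matters with 30% dropout planned.

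The cost is one model term and a sentence of text. No new data, budget or design change is needed, and the sample size can stay as it is.

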## Discussion

The first 5 years of life are critical for establishing health behaviours such as physical activity which enables children to have both a healthy childhood and decreases their risk of later chronic disease. Most young children do not have enough opportunity to be active. ECEC is a key setting to intervene to increase physical activity in the early years [41]. Physical activity has not to date, been a focus for educators or the ECEC sector, and at best provides a ‘piecemeal’ approach to physical activity promotion in early childhood. This study rectifies this situation by providing evidence of the effectiveness of the Play Active program.

The Play Active program will enable ECEC services to provide supportive policy environments that give children in their care a physically active and healthy start to life. Play Active provides ECEC services with an evidence-informed physical activity policy intervention and policy implementation support strategies to improve educator physical activity practices and positively impact children’s physical activity levels whilst attending care. Considering a large proportion of children attend ECEC, Play Active has the potential to reach a significant number of young children. With the ECEC environment accounting for almost a half of the variation in children’s physical activity levels, findings from this study are critical for informing a scale-up and adaptation of the Play Active program to improve children’s physical activity levels, health and wellbeing.

## Data Availability

A copy of the ECEC specific physical activity policy template is available from the corresponding author by email request. The de-identified datasets generated from this study will be available for analytic purposes by academics and research staff if approved by the Principal Investigator and relevant ethics committees, from 12 months following the anticipated project end date.

## Abbreviations

ECEC: Early Childhood Education and Care
NAPSACC: Nutrition and Physical Activity Self-Assessment for Child Care
EPAO: Environment and Policy Assessment and Observation
